## Methods and Analysis

### Ethical Approval and Informed Consent

Ethical approval was obtained from the Walter Sisulu University Human Research, Ethics and Biosafety Committee with approval number: 070/2021. Then the study was registered with the NIH ClinicalTrials.gov (Protocol https://ClinicalTrials.gov Identifier: NCT05091827; https://clinicaltrials.gov/ct2/show/NCT05091827). The purpose of the study will be explained thoroughly to potential participants attending the antenatal clinic in the Nelson Mandela Academic Hospital, Mthatha, Eastern Cape Province of South Africa. Pregnant women who meet the selection criteria and are willing to participate in the study will be required to sign informed consent forms for their participation and to allow their children to participate in the study from birth. Participation will be voluntary. This study will adhere to the standards of the South African National Data Protection Acts whereby the identity of the participants will be kept confidential. During data and sample collection, study ID will be assigned to participants to protect their identify and keep them confidential and anonymous. Participant's data will be stored in a secured database. After, commencement of study there will be no important changes in the methods.

### Selection Criteria

Pre-eclamptic or normotensive pregnant women with singleton, uncomplicated, between 20 and 26 weeks of pregnancy will be recruited for the study. Pregnant women with chronic hypertension, type 2 diabetes, gestational diabetes, renal and CVDs or any critical health condition will be excluded from the study. Furthermore, data will not be collected from eligible pregnant women who have performed physical exercise, smoked, or eaten for the past 6 h prior to data collection.

### Study Design and Procedure

This will be a prospective case-control study involving babies born to pre-eclamptic pregnant women and babies born to normotensive mothers recruited at the Nelson Mandela Academic Hospital, Mthatha, Eastern Cape Province of South Africa. Pregnant women who meet the selection criteria will be recruited between weeks 20–26 of gestation and their cardiovascular risk profile assessed at week 30 of gestation. The cardiovascular risk profile of their offspring will be assessed at birth and 6 weeks later.

Recruited pregnant women will be assessed at baseline (week 30 of gestation) for cardiometabolic risk profile including their PE status, anthropometry, blood pressure, oxidative stress, and vascular function. The socio-demographic, obstetric, and medical history will be collected using a structured interviewer administered questionnaire. Their blood pressure (systolic and diastolic blood pressures (BP) and heart rate, and anthropometric measures including weight and height will be measured. A vicorder (SMT Medical GmbH&Co., Wuerzburg, Germany) will be used to measure pulse wave velocity (PWV) to assess arterial stiffness and ankle-branchial index (ABI). The retinal microvasculature via retinal imaging will be assessed for vascular changes using a Optomed Aurora retinal camera (Optomed, [name], Finland). Gestational ultrasound will be performed to determine placental morphometry, architecture and vascularization. Fasting blood will be collected for the assessment of lipid profile, glycaemic, oxidative stress, reno-cardiovascular, and endothelial function markers.

At birth, the gestational age and mode of delivery of the offspring will be noted. The Appearance, Pulse, Grimace, Activity, and Respiration (APGAR) score (1–5 min) will be determined. The weight, height/length and blood pressure of the child will be measured, and PWV measured using a vicorder. Cord blood will be collected for determination of cardiometabolic risk markers including lipid profile, oxidative stress, reno-cardiovascular and endothelial function markers. Six weeks after birth, blood pressure (BP) and anthropometric measurements and PWV assessment will be done in children. Then, blood and urine samples will be collected for the assessment of endothelial function, lipid profile, reno-cardiovascular and oxidative stress markers.

All pregnant women eligible for the study will be required to fast overnight and will be asked to restrain from smoking, drinking coffee, and physical exercise for 4–6 h prior to assessments. Recruitment of pregnant women at the hospital will commence in October 2021. The pregnant women will be followed-up for a period of 1 year. After delivery, follow-up of their offspring will commence in November 2022 and span through February 2023. Data collection and analysis will be completed by April 2023. The study design along with the various assessments and timeline are summarised in Figures 1, 2 respectively.

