### Statistical Analysis

STATA (Stata, College Station, Texas, USA) and IBM statistical package for social sciences (SPSS) Version 23.0 (IBM Corp). Armonk, NY, USA) will be used for data analyses. The Shapiro-Wilks test will be used to check for normality and data will be log-transformed and/or corrected for outliers when necessary. Descriptive statistics will be employed for data presentation as mean ± standard deviation (SD) or median ± interquartile range (IQR) for continuous variables and proportions (percentages) for categorical variables. Independent sample *t*-test will be used to compare mean differences between groups (pre-eclamptic and normotensive pregnant women and their offspring). Multivariate analysis using multiple analysis of variance (MANOVA) will be used to compare continuous variables for two or more independent variables where necessary. Chi-square test of association and Pearson correlation will be used to assess the relationship between cardiometabolic risk factors and PE at baseline and follow-up for both mother and child. A difference will be considered significant at α = 0.05.

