## Discussion

This study aims to investigate the relationship between PE and cardiovascular risk in children born to pre-eclamptic mothers in a rural South African population of African descents. It has been suggested that the foeto-placental vascular endothelial dysfunction may cause epigenetic alteration in the intrauterine environment of the foetus (39). Therefore, the maternal gestational environment may be programmed to have a significant impact on foetal and offspring health later in life (9). In fact, some studies have undertaken to investigate whether children born to pre-eclamptic mothers may predispose them to cardiovascular risk factors. Miller et al. demonstrated as early as 1983 that full-term neonates born to pre-eclamptic mothers have transient hypertension during the first hours of life (40). A meta-analysis study with over 45,000 individuals reported a 1.35 mmHg and 2.39 mmHg higher DBP and SBP in children and young adults born to pre-eclamptic pregnancies (41). The timing of the onset of PE has been reported to be a determinant of hypertension in offspring later on in life as offspring born to mothers with early PE onset were found to have increased central and peripheral SBP (6 mmHg) (42). Also, offspring of pre-eclamptic pregnancies showed a distinct vascular phenotype which could possibly mediate increased risk of hypertension in future (13). More so, impaired flow mediated endothelial responses as well as increased carotid intima-media thickness which suggest endothelial dysfunction was observed in preterm-born young adults exposed to a hypertensive pregnancy (12). A Spanish study on *in-utero* growth restricted children showed that children born to pre-eclamptic parents had higher BP, cardiac remodeling, and evidence of endothelial dysfunction at 6 months of age. Follow-up studies on school age children showed that they had higher SBP and DBP, smaller hearts, increased heart rate and features of cardiac diastolic dysfunction (43). A Norway study of 15,778 participants of which 343 were born to pre-eclamptic mothers showed increased BP, body mass index, wider waist circumference, higher non–HDL-cholesterol and triglycerides suggesting increased risk of CVDs (44). All these studies have shown that children born to pre-eclamptic mothers are prone to obesity, hypertension, diabetes and CVDs in their adult life (45, 46). However, all these findings were established in western populations with little or no reports from children of African origin. To our knowledge there is yet to be such a study in an African population. Conversely, it remains unclear whether the high prevalence of cardiovascular risk factors (obesity, hypertension etc) observed in South African children of African ancestry (47, 48) may have originated from pre-eclamptic mothers. The assessment of cardiovascular risk in pre-eclamptic pregnant women and the follow-up of their offspring after birth for possible cardiovascular risk may address this concern.

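### Infant outcomes are compared without regard to gestational age at birth, so if case infants are born earlier, the raw contrasts mix pre-eclampsia exposure with immaturity at measurement.

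*Protocol article*

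**What the plan says.** Under Study Design and Procedure, both infant time points are counted from delivery: "The cardiovascular risk profile of their offspring will be assessed at birth and 6 weeks later". The second is repeated in the procedure: "Six weeks after birth, blood pressure (BP) and anthropometric measurements and PWV assessment will be done in children". The birth measurements are listed as "The weight, height/length and blood pressure of the child will be measured, and PWV measured using a vicorder", with no mention of size for gestational age. Cord blood at birth, and blood and urine at six weeks, supply the biomarkers. On maturity the section says only: "At birth, the gestational age and mode of delivery of the offspring will be noted".

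Selection Criteria fixes gestation at recruitment, not at delivery: "Pre-eclamptic or normotensive pregnant women with singleton, uncomplicated, between 20 and 26 weeks of pregnancy will be recruited for the study".

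Statistical Analysis gives the between-group method: "Independent sample *t*-test will be used to compare mean differences between groups (pre-eclamptic and normotensive pregnant women and their offspring"). It adds that MANOVA "will be used to compare continuous variables for two or more independent variables where necessary", and names no covariate. Log-transformation and outlier correction are allowed, but neither deals with maturity. The limitations in the Discussion do take up confounding, and there the only candidates named for the analysis are drugs taken for a long time in pregnancy.

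**The concern.** At a visit fixed by time since birth, an infant's maturity (postmenstrual age) is gestational age at birth plus a constant: 0 weeks at the birth visit, 6 weeks at the second. Any difference between the groups in mean gestational age therefore carries over in full to both visits. The unadjusted contrast then has two components: what pre-eclampsia exposure does at a given maturity, and what being less mature does to the reading.

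Three aims are affected. For blood pressure, PWV and biomarkers, a difference or a null cannot be assigned to either component. For weight and length, a raw deficit could mean a baby small for its gestational age or one simply born early, although the Introduction ties cardiovascular risk to small-for-gestational-age. The listed objective of change from birth to six weeks would cover different stretches of maturation in the two groups.

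**Working it through.** **Step 1. What the visit rule does to maturity.** Postmenstrual age at the visit = gestational age at birth + 0 or 6 weeks. The records below are illustrations, not data from the documents.

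| Infant | Birth reading | Six-week reading |
|---|---|---|
| Control born at 39 weeks | 39 | 45 |
| Case born at 33 weeks | 33 | 39 |
| Case born at 31 weeks | 31 | 37 |

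A case born at 33 weeks has its six-week reading at the maturity of the 39-week control's birth reading. A case born at 31 weeks is still two weeks short of it. Nothing in Selection Criteria keeps such infants out, and both births fall after the week-30 maternal assessment.

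**Step 2. Planning values, from Sample Size Calculation.** Diastolic means are 42.11 and 30.17 mmHg, so the difference is 42.11 − 30.17 = 11.94, as printed. The group SDs are 11.49 and 11.89, so pooled SD = √((11.89² + 11.49²)/2) = 11.69 mmHg. There are 49 completers per group. The SD of 0.05 printed among the calculation inputs is a separate matter and is not used here.

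**Step 3. Possible size of the maturity component.** Bias = slope × mean gestational-age gap. Neither is in the documents. Assumed ranges: gap 1–7 weeks, slope 0.5–1.5 mmHg of diastolic pressure per week. Entries are mmHg, with the share of 11.94 in brackets.

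| Gap (weeks) | Slope 0.5 | Slope 1.0 | Slope 1.5 |
|---|---|---|---|
| 1 | 0.5 (4%) | 1.0 (8%) | 1.5 (13%) |
| 3 | 1.5 (13%) | 3.0 (25%) | 4.5 (38%) |
| 5 | 2.5 (21%) | 5.0 (42%) | 7.5 (63%) |
| 7 | 3.5 (29%) | 7.0 (59%) | 10.5 (88%) |

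If diastolic pressure rises with maturity, as the positive slope assumes, this component lowers the case readings.

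**Step 4. What the t-test would show if the groups did not differ at equal maturity.** With 49 per group, SD 11.69 and two-sided alpha 0.05 (noncentral t), the rejection rate is 5.5% for a 0.5 mmHg component, 24% for 3 mmHg, 55% for 5 mmHg and 99% for 10.5 mmHg. So the issue ranges from negligible to dominant, depending on two figures that the documents do not give.

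**Step 5. Precision cost of adjusting.** In a regression on group and gestational age, the standard error of the group term is multiplied by √(1 + (gap²/4)/s²), where s² is the mean within-group variance of gestational age. This ignores any residual variance that gestational age explains. Assuming SDs of 1.5 weeks (controls) and 3 weeks (cases), s² = (2.25 + 9)/2 = 5.625. Gaps of 3, 5 and 7 weeks give factors of 1.18, 1.45 and 1.78.

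**The case against.** **A condensed article leaves covariates to the full plan.** In part this stands. Gestational age is collected, multivariable analysis is allowed, and standardised values are not ruled out. But the article fixes the visit timing and the offspring test, and where it does discuss confounding it names only drugs.

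**The article does not say that cases are born earlier.** This stands. The Discussion's vascular finding that "was observed in preterm-born young adults exposed to a hypertensive pregnancy (12" describes who was in that sample, not an effect of pre-eclampsia on gestation. Small-for-gestational-age is size relative to gestation, not early birth. The Discussion also cites full-term neonates of pre-eclamptic mothers. Even the case definition is unsettled: Selection Criteria recruits pre-eclamptic women at 20–26 weeks, while Study Design and Procedure assesses pre-eclampsia status at week 30. Earlier delivery is a plausible premise, not a documented one.

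**Visit timing is not a separate fault.** This stands. Postmenstrual age differs from gestational age at birth by a constant at each visit, so the point is about missing gestational-age adjustment and not about a wrong schedule.

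**The raw contrast is a legitimate answer.** This stands. Earlier delivery may be one route by which pre-eclampsia acts on the infant. The raw contrast then estimates the total effect, and conditioning on a mediator changes the question and can introduce bias.

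**A reader might infer a power loss** by subtracting a maturity component from 11.94 mmHg. The documents do not support that. The planning difference is a contrast between neonates of pre-eclamptic and normotensive mothers with no gestational-age adjustment mentioned, so it may already contain any maturity deficit, and subtracting it again would count it twice.

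**Conclusion.** The point holds in a limited form. Followed as written, the plan cannot separate pre-eclampsia exposure from immaturity at measurement if the groups differ in gestational age at birth, and raw weight and length cannot separate small-for-gestational-age from early birth. That much follows from the visit timing, the unadjusted t-test, the open eligibility on gestation at delivery, and the lack of any stated use of the recorded gestational age.

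The size and direction do not follow from the documents. The 0.5–10.5 mmHg range rests on an assumed gap of 1–7 weeks and an assumed slope of 0.5–1.5 mmHg per week, and at the low end the effect is minor.

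A reader might also infer that the offspring results would be uninterpretable, or that a difference counts as an effect of pre-eclampsia only if it survives adjustment. Neither is supported: the article's aim is the relationship between pre-eclampsia and offspring risk, and a total-effect contrast addresses it. What is missing is a statement of which effect is meant, and the companion analysis that would show how much of it persists at equal maturity. This is a worthwhile improvement, not a flaw that invalidates the design.

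**What to change.** Keep both visits and the t-test, and make four additions to the analysis text.

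1. Label the raw between-group contrast as the total effect of pre-eclampsia, including any effect through earlier delivery.
2. Beside each raw comparison of infant blood pressure, PWV and biomarkers, report a linear regression on group and gestational age at birth (equivalently, postmenstrual age at the visit).
3. Beside raw weight and length, report weight- and length-for-gestational-age z-scores at birth and corrected-age z-scores at six weeks.
4. Report the gestational-age distribution by group. Interpret the adjusted contrast as the difference at equal maturity, with two caveats: earlier delivery may be a mediator, and limited overlap in gestational age would make the linear adjustment lean on extrapolation. Do not use it as a gate for attributing an effect to pre-eclampsia.

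The cost is analysis wording and some extra table rows, since gestational age at birth is already recorded. The statistical price is a wider interval for the adjusted contrast, with a standard error about 1.2–1.8 times larger at gaps of 3–7 weeks under the SDs assumed in the working. That is a reason to report it alongside the raw contrast and not in its place.

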### Sample Size Calculation

The sample size was calculated with reference to the study by Amini et al. who showed BP differences between neonates from normotensive and pre-eclamptic mothers (28). The difference in systolic BP (SBP) was very high in pre-eclamptic mothers (68.2 ± 1.49 mmHg) compared to normotensive mothers (49.85 ± 5.49 mmHg). Because of the very high SBP variance and standard deviation in the pre-eclamptic group, we decided to use the diastolic blood pressure (DBP) values (normotensive: 30.17 ± 11.89 mmHg vs. pre-eclamptic: 42.11 ± 11.49 mmHg) for the sample size calculation. The software-R, version 4.1.0 (R Core Team, St. Louis, Missouri, USA) was used for the sample size calculation with parameters: alpha = 0.01, mean difference = 11.94 and standard deviation = 0.05. The calculated total sample size is 98 (49 cases and 49 controls). We assumed that not all participants would return for the follow-up and therefore adjusted our sample size by 20% to compensate for possible loses to follow-up. Thus, the total sample will be 98/(100–20/100) = 122 neonates. This implies that the study will commence with the recruitment of 122 pregnant women (61 pre-eclamptic women and 61 normotensive pregnant women) who meet the selection criteria.

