### Assessment of Arterial Stiffness and Ankle-Branchial Index

A vicorder device (SMT Medical GmbH&Co., Wuerzburg, Germany) will be used for the assessment of pulse wave velocity (PWV), a measure for arterial stiffness and ankle-brachial index (ABI). Brachio-femoral PWV will be done as reported by Alwan et al. (32). Prior to PWV measurements, participants will be asked to lie in a supine position and rest for 10 min. Thereafter, a standard 10 cm pressure cuff will be placed on the upper right thigh as high as possible toward the crotch while another thin pressure cuff will be placed around the neck just on the carotid artery. The distance between the neck and thigh cuffs will be measured in cm using a measuring tape. Pressure lines: red pressure line to the neck cuff and blue pressure line to the thigh cuff, will be connected to the vicorder. Participants details including the BP, weight, height, and length between the carotid and femoral arteries will then be entered into the vicorder software and the test will be conducted. The PWV (m/s) will be calculated as a ratio of path length (between carotid and femoral arteries) and transit time. Prior to the measurement of ABI, a pressure cuff will be placed around the right arm of the participant and another pressure cuff around the ankle of the same side of the body. Participants details (BP, weight, and height) will be entered into the vicorder software while fixing the target SBP of 200 mmHg and the test conducted. The ABI will be calculated as the ratio of the SBP of the ankle and branchial regions.

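### Infant PWV, labelled a stiffness measure, is compared without adjustment between groups planned to differ by 11.94 mmHg in neonatal diastolic pressure, so a difference at birth could reflect pressure alone

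*Protocol article*

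**What the plan says.** Study Design and Procedure schedules pressure and PWV together in the infant at both visits. At birth: "The weight, height/length and blood pressure of the child will be measured, and PWV measured using a vicorder". Later: "Six weeks after birth, blood pressure (BP) and anthropometric measurements and PWV assessment will be done in children".

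The section on arterial stiffness and ankle-brachial index describes the method as "assessment of pulse wave velocity (PWV), a measure for arterial stiffness". The calculation is given as: "The PWV (m/s) will be calculated as a ratio of path length (between carotid and femoral arteries) and transit time". That formula has no pressure term. Blood pressure does enter the device ("Participants details including the BP, weight, height, and length between the carotid and femoral arteries will then be entered into the vicorder software"), but only as a participant detail; no pressure correction of the result is described.

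Statistical Analysis says that the independent-sample t-test "will be used to compare mean differences between groups (pre-eclamptic and normotensive pregnant women and their offspring"). MANOVA is to be used where necessary, with no covariate named. The only confounder named anywhere is long-duration medication, in the limitations part of the Discussion.

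Sample Size Calculation takes neonatal diastolic pressure as 30.17 (SD 11.89) mmHg in the normotensive group and 42.11 (SD 11.49) mmHg in the pre-eclamptic group, and plans on "mean difference = 11.94".

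**The concern.** PWV depends on the pressure distending the artery as well as on the properties of the wall. This is general arterial physiology and is not stated in the article. If the planning assumption is right, the infant groups will be clearly separated on pressure at birth, and some difference in raw PWV is then expected even if the arteries are the same.

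The risk is that one finding, higher infant blood pressure, is reported twice: once as pressure and again as stiffness. The Discussion presents vascular function in exposed children of African ancestry as a first. It also rules out flow-mediated dilatation, and retinal imaging is listed only for the women. PWV is therefore the only physical measure of arterial function listed for the infants, and a claim of vascular change programmed before birth would lean on it heavily.

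The infant pressure comparison itself is not in question. The infants are not selected on their own pressure.

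**Working it through.** **Inputs from the article**
- Diastolic pressure 30.17 (SD 11.89) against 42.11 (SD 11.49) mmHg.
- 49 per group as calculated; 61 per group as recruited.
- Analysis alpha 0.05.

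**Step 1: the planned pressure gap.** 42.11 − 30.17 = 11.94 mmHg, which reproduces the article's figure. Pooled SD = √((11.89² + 11.49²)/2) = 11.69 mmHg. Standardised gap d = 11.94/11.69 = 1.02. With 49 per group, two-sided power to detect this gap is about 99% at alpha 0.01 and 99.9% at 0.05. The design therefore expects the groups to differ visibly in pressure when PWV is compared.

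**Step 2: assumptions.** The article gives no infant PWV SD, slope or correlation. Let r be the within-group correlation of PWV with diastolic pressure, taken from 0.1 to 0.5. Suppose pre-eclampsia has no effect on PWV at equal pressure.

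**Step 3: raw PWV difference due to pressure alone.** In units of the within-group PWV SD, the shift is r × d = 1.02r. With n per group the noncentrality of the t-test is 1.02r × √(n/2). For r = 0.3 and n = 49 this is 0.306 × 4.95 = 1.52, against a critical value of 1.98 on 96 degrees of freedom.

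| r | Shift (PWV SDs) | Significant at 0.05, 49 per group | Significant at 0.05, 61 per group |
|---|---|---|---|
| 0.1 | 0.10 | 8% | 9% |
| 0.2 | 0.20 | 17% | 20% |
| 0.3 | 0.31 | 32% | 39% |
| 0.4 | 0.41 | 52% | 61% |
| 0.5 | 0.51 | 71% | 80% |

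**Step 4: the same data with pressure as a covariate.** In 4,000 simulated studies with 49 per group, a linear model with group and diastolic pressure found a significant group effect in 4.7% at each of r = 0.2, 0.3 and 0.5. The raw t-test in the same simulations gave 17%, 32% and 70%.

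**Step 5: precision cost of the covariate.** Squared correlation of group with pressure = d²/(d² + 4) = 1.043/5.043 = 0.207. Variance inflation = 1/(1 − 0.207) = 1.26. Standard error factor = √1.26 = 1.12, so about 12% wider before any gain from lower residual variance.

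**Step 6: sensitivity to the size of the gap.** The 11.94 mmHg is a neonatal figure, and no 6-week value is given. The Discussion cites a diastolic difference of 1.35 mmHg in children and young adults. Purely as an illustration of a small gap, using the same SD, d = 1.35/11.69 = 0.115. The shift for r = 0.1 to 0.5 is then 0.01 to 0.06 PWV SDs, and the raw t-test with 49 per group is significant in 5.0% to 5.9% of studies, close to nominal.

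**The case against.** **The raw comparison answers the stated aim.** The aim is to compare the cardiovascular risk profile of the offspring, not to isolate wall stiffness at equal pressure. Infant pressure arises after the exposure and may lie on the path from pre-eclampsia to PWV, so the unadjusted difference is a valid total difference. This stands. A reader might infer that the planned t-test is invalid or should be replaced; the documents do not support that. The trouble is only in reading its result as stiffness.

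**The article makes no explicit stiffness claim for infants.** Where Study Design and Procedure links PWV to stiffness, it is describing the women, and the Discussion speaks of vascular function. This is partly right. However, the methods section on the device calls PWV a measure of arterial stiffness in general and offers no other reading for infants.

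**Adjustment can remove a real effect.** Stiffer arteries may themselves alter pressure, so conditioning on pressure can take away part of a true vascular difference. This stands, and it is why the adjusted estimate should not be the sole basis for every statement about vascular function.

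**Covariates may be left to a fuller plan.** The intention to treat drugs as a confounder suggests that some adjusted modelling is planned. Still, the point rests on what the article does state: a t-test, a stiffness label and a planned pressure gap.

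**The effect in infants is not documented.** True; hence the range. A reader might infer from a steep slope that a spurious result is almost certain. An assumed 0.06 m/s per mmHg would imply r = 0.06 × 11.69/0.8 = 0.88 at a PWV SD of 0.8 m/s, and an impossible 0.06 × 11.69/0.6 = 1.17 at 0.6 m/s. Near-certainty is not a supportable figure.

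**Conclusion.** The point holds for the birth visit. The plan expects a neonatal diastolic gap of 11.94 mmHg (about 1.02 SD) and compares a pressure-dependent measure, labelled as stiffness, without taking that gap into account. A significant PWV difference at birth could therefore reflect pressure alone.

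The size rests on an assumed within-group correlation of 0.1 to 0.5, no group effect at equal pressure, and 49 per group. On those terms the raw t-test is significant in about 8% to 71% of studies, or 17% to 32% for correlations of 0.2 to 0.3, against about 5% with pressure in the model.

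A reader might carry the same figures to 6 weeks. The documents do not support that: they give no 6-week pressure difference, and the Discussion cites work describing neonatal hypertension after pre-eclampsia as transient. At 6 weeks the problem is as large as whatever gap remains.

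**What to change.** In Statistical Analysis, keep the raw infant PWV comparison and describe it as the total difference between groups. Beside it, at birth and at 6 weeks, report a linear model of infant PWV on group and the infant's own blood pressure from the same visit. Name one pressure measure in advance, for example mean or diastolic pressure. State that a pressure-independent difference in infant arterial stiffness will be claimed only if the adjusted estimate supports it, and that blood pressure may lie on the causal path.

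The cost is a few sentences and one extra model per visit on data already being collected. If the planned gap holds, the standard error of the group effect widens by about 12% before any gain from lower residual variance. The adjusted model may also remove part of a real vascular effect, so both estimates need to be shown.
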